## Abstract

Unmet health-related social needs (HRSNs) are major drivers of poor health outcomes in early childhood. Children with unmet HRSNs are at greater risk for developmental delays, caregiver stress, and increased healthcare utilization, yet current screening approaches in pediatric primary care are resource-intensive and inconsistently implemented. AI-powered chatbots (conversational agents or virtual assistants) may offer a private, secure, scalable, and cost-effective alternative for identifying unmet needs and connecting families to services. This protocol describes a pilot randomized controlled trial designed to evaluate the feasibility, acceptability, and usability of DAPHNE, an AI-driven chatbot developed to facilitate the identification of unmet HRSNs and provide personalized community resource referrals. One hundred caregivers of children under two years of age will be recruited from Nationwide Children’s Hospital pediatric primary care clinics and randomized to either the standard care (control) group or DAPHNE+ Standard care (intervention) group (n = 50 each arm). Caregivers will complete surveys at baseline, 1 month, 3 months, and 6 months post-intervention (depending on the measure). For the intervention group, participants will receive weekly chatbot prompts and on-demand access throughout the 6-month study period. Primary outcomes include study feasibility (recruitment, retention, and survey completion across both arms), acceptability (caregiver-reported ratings in both arms and intervention-specific ratings), and usability of the DAPHNE chatbot (System Usability Scale among intervention participants). Secondary outcomes includes caregiver-reported outcome measures (caregiver stress, self-efficacy, satisfaction with resource access, quality of life), and electronic health record-derived measures (including documentation of HRSN screening and referrals, adherence to well-child visits, missed appointments, emergency department utilization, and estimated healthcare costs). In addition, ten primary care providers will also participate to assess workflow integration and report on current HRSN practices. Mixed-methods analyses will integrate survey data, chatbot engagement metrics, and qualitative interviews to refine both the intervention and the study protocol. The results of this study will inform the design of a future multi-site trial to evaluate the efficacy and implementation of DAPHNE for addressing HRSNs in pediatric primary care. Trial registration: NCT07168382.

## Introduction

Health-related social needs (HRSNs), including food insecurity, unstable housing, transportation challenges, and financial instability, account for more than 50% of modifiable health outcomes [1,2]. Children with unmet HRSNs have substantially elevated risks for cognitive, behavioral, and developmental difficulties, having greater risk than peers from resource secure households [3–6]. They are also 18% more likely to have emergency department (ED) visits and 36% more likely to experience hospitalizations compared with children without social risks (IRR = 1.18, 95% CI [1.12–1.23]; 1.36, 95% CI [1.26–1.47]) [7]. This burden is especially pronounced among infants younger than 2 years, for whom early-life HRSNs, such as food insecurity or benefit instability, are linked to measurable behavioral and regulatory difficulties by six months of age (aOR= 1.64–1.86 across domains; aOR= 2.16 for 2 or more identified HRSNs) [8]. This early-life concentration represents a high-yield prevention target and reinforces primary care as the locus for proactive screening and linkage to services [7–9].

Pediatric primary care clinics (PCCs) are therefore critical access points for early identification and intervention but current screening practices are constrained by staffing shortages, workflow inefficiencies, and high operational costs [10]. Caregivers are also often reluctant to disclose needs due to stigma, language barriers, or confusion about service navigation, which further exacerbates under-identification [11]. Referral completion is constrained by a combination of structural, provider-level, and caregiver-level barriers. Structural barriers include complex eligibility requirements, poor coordination, and limited availability of community resources. Provider-level barriers, such as limited familiarity with available services and uncertainty about referral processes, further hinder follow-through. Caregivers also face barriers related to time, transportation, and competing demands that make service access difficult [12–14].

Despite the availability of standardized screening instruments, fewer than 25% of hospitals and 16% of physician practices routinely screen for HRSNs [15]. When implemented, screening is often limited to episodic encounters such as annual well-child visits, missing acute and urgent social needs at other timepoints [16,17]. In this cohort, particularly the caregivers of infants (ages 0–2) are disproportionately affected by the lack of screening [3,8]. For instance,food insecurity in this age group is strongly associated with adverse developmental outcomes [18], higher hospitalization rates [19], and increased risk of chronic conditions including obesity and diabetes [20]. The barriers are particularly pronounced for Medicaid-insured children, who experience greater challenges in securing basic necessities such as infant formula, diapers, and transportation [21,22].

### Rationale for AI-driven solutions

AI-based chatbots (also known as conversational agents and virtual assistants) offer an opportunity to overcome some of these structural and provider-related barriers in HRSN identification and referral. Unlike traditional clinician-initiated screening, chatbots can provide continuous, user-initiated engagement across multiple contexts and time points, enabling real-time identification of urgent needs [23–25]. By facilitating private conversations, chatbots play a positive role to reduce stigma and support honest disclosure for some groups [11,26–28]. They can also automate referrals using up-to-date community resource databases, and reduce provider burden while offering tailored, context-specific recommendations [25,29,30]. These advantages are further supported by our preliminary engagement sessions with social work teams, caregivers, and patient advocates, who indicated high acceptance of chatbot-based social needs assessment, provided that privacy and usability are prioritized [23,31].

### Conceptual framework

The methods for this study were informed by the Obesity-Related Behavioral Intervention Trials (ORBIT) model [32,33], which provides a systematic framework for developing behavioral interventions by progressing through iterative phases (from early conceptualization and definition of intervention components, to feasibility and pilot testing, and ultimately to efficacy and effectiveness trials). Prior applications of conversational AI in healthcare, including tools for mental health support, symptom tracking, and caregiver-facing applications, demonstrate early evidence and implications for digital engagement strategies [34–39]. Building on this foundation, the present pilot randomized controlled trial (pRCT) corresponds to Phase IIb of ORBIT, which emphasizes feasibility testing, establishing acceptability, and refinement of study protocols before progression to full-scale efficacy trials.

### Study objectives

The long-term goal of this research is to develop an empirically supported, scalable, AI-driven solution to facilitate HRSN identification and referral in pediatric primary care. This pilot study has three specific objectives: (1) To assess the feasibility, acceptability, and usability of the DAPHNE chatbot with caregivers and providers of pediatric primary care patients compared with standard care; (2) To evaluate the feasibility and acceptability of the study protocol, including recruitment, retention, and measurement strategies, for informing design of a future large-scale trial; and (3) To characterize the current standard of care for addressing unmet HRSNs, thereby informing selection of appropriate comparator conditions and outcomes in future trials.

### Preliminary work

We have conducted several studies to inform DAPHNE’s development. A scoping review of patient-facing chatbots and voice agents revealed high interest but a lack of rigorous trials on chatbot-based interventions and indicating the need for systematic evaluation [40]. Building upon this knowledge, we developed a voice-interactive diary for caregivers of children with special health care needs; over 80% reported ease of use and approximately half increased health tracking frequency, demonstrating caregiver receptivity to conversational tools [39]. To enable integration of unstructured caregiver data, we created a natural language processing pipeline that accurately structured caregiver-generated notes and transcripts (F1 > 0.7), validating real-time data capture for clinical use [41,42]. Finally, in a feasibility study of a semi-functional DAPHNE prototype (n = 13), community health and social workers rated usability at 72/100 on the System Usability Scale and emphasized its value for triaging referrals [23]. Together, these studies establish feasibility, provider and caregiver acceptance, and the need for a pilot randomized controlled trial.

## Methods

### Study design and setting

This study is designed as a pilot randomized controlled trial (pRCT) guided by the ORBIT model (Phase IIb) [32,33]. One hundred caregivers of children (prioritizing ≤2 years of age) will be recruited from Nationwide Children’s Hospital Primary Care Network (NCH PCN). Following baseline assessment, participants will be randomized in a 1:1 ratio to either the standard care group or DAPHNE + standard of care group (n = 50 per arm). In addition, 10 providers will be recruited to complete surveys on workflow integration and HRSN practices.

The trial will be conducted in NCH PCCs, which provided nearly 250,000 visits in 2024 for mostly Medicaid-enrolled patients. The PCN includes 14 clinics across the Columbus metropolitan area. For the purpose of this study, we identified clinics with the capacity to support the research project and a relatively higher number of patients with unmet HRSNs.

### Ethics

The study has Institutional Review Board (IRB) approval at Nationwide Children’s Hospital (#00004369). Informed consent will be obtained from all participants. For Electronic Health Records (EHR) data extraction, consent for the child’s participation will be obtained by one parent. If recruited, children 9 and above will provide informed assent before research procedures begin.

### Study status and timeline

This study is currently in the Initiation and Planning phase, with the protocol finalized and Institutional Review Board (IRB) approval obtained (NCH IRB #00004369). We initiated the process of participant recruitment in Q1, Year 1, and are actively enrolling participants. The time schedule is provided in Fig 1. We project that participant recruitment will be completed in Q2 of Year 2, primary data collection (6-month follow-up) will be completed in Q1 of Year 3, and final results are expected for manuscript submission in Q4 of Year 3.

**Fig 1 pone.0337868.g001:**
[figure not shown]
Time schedule of enrollment, interventions, and assessments on participant outcome (informed by the SPIRIT 2025 reporting guideline; S1 Checklist) [43].

### Participants

Caregivers. Recruitment will occur through the NCH PCN, with research staff approaching caregivers during routine visits. Our target recruitment is n = 50 participants per arm, facilitated using flyers and social worker referrals. Furthermore, we will communicate with potential participants who are interested via virtual methods (phone call, teleconference). Inclusion criteria are: (1) primary caregiver of a child (prioritizing ≤2 years old) receiving care at the selected clinics in the PCN, (2) self-identify with at least one unmet HRSN (3) ability to provide informed consent and complete study surveys in English, (4) ownership of a mobile device for chatbot use, and (5) willingness to participate in follow-up assessments. Exclusion criteria: none beyond failure to meet the above criteria. Caregivers will be compensated for their participation.

#### Providers.

To evaluate the feasibility of integrating the DAPHNE chatbot into clinical workflows at primary care clinics, we will recruit approximately 10 providers across the NCH PCN, ensuring representation from at least 50% of the 14 PCC sites. Eligible providers include physicians, nurses, social workers, and care coordinators who are directly involved in patient care. Providers on extended leave or those not engaged in patient care will be excluded. Recruitment will be facilitated through the NCH Primary Care Research Network.

### DAPHNE Chatbot development and structure

DAPHNE was developed using secure cloud infrastructure (via AWS). At the backend, we integrated state-of-the-art large language models (e.g., Claude, GPT, Mistral, Gemini, LLaMA) adapted for healthcare settings and enabling intent recognition, contextual follow-up, and dynamic retrieval of resources from the resources API. Unlike rule-based decision trees, the AI allows free-text input from caregivers, interpreting varied language patterns (e.g., “I can’t get to the clinic” means transportation needs) and providing tailored responses. It demonstrated >99% intent accuracy over 1,500 turns of conversations [31].

DAPHNE is provided as a web-based conversational agent accessible on iOS, Android, or web browsers (Fig 2). It is deployed using HIPAA-compliant servers and validated for accuracy and security by the internal Information Services governance committee. The chatbot will not require computational power on the user’s side, therefore a simple smartphone could be used to engage with the app. Our conversational model is also optimized for scaling at the cloud side with minimal cost and computational resource needs.

**Fig 2 pone.0337868.g002:**
[figure not shown]
Overview of the DAPHNE chatbot connecting users to community resources. Created in BioRender. [name] (2026) https://BioRender.com/n6anxpk.

To ensure safety, DAPHNE automatically flags out-of-scope or potentially concerning interactions, and all conversations are subject to monitoring and auditing protocols. The research team reviews flagged transcripts to prevent harmful content and safeguard patient well-being. In addition, the research team periodically reviews the chatbot logs. For urgent or high-risk needs, an escalation protocol is used directing caregivers to professional resources, while the research team coordinates with the social work team as appropriate.

### Scope of HRSN and DAPHNE chatbot

The chatbot’s scope is intentionally bounded and aligned with nationally recognized HRSN screening frameworks used in primary care, including guidance from SIREN, the PhenX Toolkit social determinants measures, and CMS Accountable Health Communities domains [44–46]. DAPHNE focuses on four predefined domains: (1) food insecurity and essential nutritional needs (e.g., infant formula), (2) housing instability, (3) transportation barriers, and (4) financial strain and material hardship (including utilities).

Conversational inputs are mapped to these predefined categories using structured intent classification, and referrals are limited to domain-specific community resources retrieved through a community resource database [47]. Domains outside this scope (urgent needs, high risk cases; e.g., interpersonal violence, mental health crisis, evictions and urgent food access) trigger an escalation protocol directing caregivers to appropriate professional or emergency services. This bounded framework ensures conceptual clarity, safety, and alignment with established HRSN screening practices and services in pediatric primary care.

### Intervention: DAPHNE Chatbot

Caregivers randomized to the intervention arm will receive onboarding consisting of instructions on how to download the app and a brief tutorial on the app’s features. The chatbot engages caregivers in natural conversations to understand HRSNs, provide tailored resource recommendations (e.g., food pantries, housing, transportation), and follow-up with automated reminders. Features include periodic personalized notifications (e.g., informational quick tips, updates), information about local services, and guidelines to sustain engagement.

### Sequence generation and concealment

The randomization sequence will be generated by the study member who is not involved in recruitment using the NCI Clinical Trial Randomization Tool (maximal procedure; maximum tolerated imbalance = 2) [48]. The sequence will be uploaded into the REDCap randomization module with role-based access controls [49]. Research staff conducting eligibility screening and baseline assessments will not have access to the allocation list. Assignment will be released automatically by REDCap only after completion of baseline measures and confirmation of eligibility, preventing prediction of future assignments. Only the intervention coordinator responsible for onboarding will be notified of allocation after assignment release.

### Control: Standard care

Caregivers in the control arm will receive the existing clinic-based HRSN screening and referral procedures as currently implemented, without access to the chatbot. These caregivers will complete the same study assessments as the intervention group except those related to chatbot usability and feasibility of the intervention.

### Contamination and standard care

To minimize contamination, intervention access will be restricted to unique participant credentials, and control participants will not be provided DAPHNE links or onboarding materials. At each follow-up assessment (1, 3, and 6 months), participants will be asked whether they have used DAPHNE outside the study or accessed any other digital HRSN screening tools. Any reported cross-exposure will be documented.

Usual care will be characterized and documented systematically. At study initiation, we will document clinics describing current HRSN screening instruments, workflow roles (e.g., medical assistant, nurse, social worker), timing of screening, referral pathways, and EHR documentation practices (where applicable). In addition, EHR abstraction will include primary care visits, number of missed appointments, number of ER visits, HRSN screening and referrals (social work encounters) for all participants. Follow-up calls with caregivers in the standard care arm will capture services received outside the health system (e.g., community-based referrals not documented in the EHR). These procedures will allow comparison of intervention and standard care exposure.

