#### Secondary outcomes.

Secondary outcomes address caregiver- and provider-level effects. Caregiver-reported outcomes (cPROMs) include stress [55], self-efficacy [56], satisfaction with access to community resources [57], and quality of life for caregiver and child as proxy [58]. These cPROMs will be completed by caregivers in both arms at baseline, 3, and 6 months. In addition to cPROMs, caregivers in both arms will complete the standardized HRSN screener. This survey will be administered at 3 and 6 months to capture changes in reported needs over time. Caregiver engagement with the chatbot is measured through system logs (e.g., minutes of use, number of logins, session durations, screenings completed, and resources accessed). Caregiver burden associated with study procedures will be measured in both arms using the Participant Burden Assessment (PeRBA; target ≥4) at 1, 3, and 6 months [59]. Provider perspectives on workflow integration will be assessed using the Workflow Integration Expectancy tool, with a target rating ≥ 4 [60]. These secondary outcomes will be analyzed to see how they change over the course of the trial and to eventually address whether there are any associations with outcome changes and chatbot use.

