#### Exploratory outcomes.

Exploratory analyses will focus on healthcare utilization and economic outcomes to inform future large-scale trials. Electronic health record (EHR) data will be extracted to capture documentation of HRSN screening and referrals, adherence to well-child visits, missed appointments, emergency department utilization, and estimated healthcare costs. EHR data will be abstracted for all participants at 3- and 6-month follow-up period to capture pediatric primary care visits, social work referrals, and emergency department utilization. Billing and visit data will be used to estimate healthcare costs, including cost avoidance from reduced no-shows or ED visits. While the study is not powered to detect cost effects, descriptive comparisons between the DAPHNE and standard care arms will be conducted to identify patterns in service utilization and associated costs. Findings will inform the selection of economic outcomes and power calculations for a future NIH R01 trial. Additional exploratory outcomes will include continuous tracking of recruitment rates and dropout rates throughout the study period. Outcome measures, descriptions and planned timeline are also available at our registered protocol [61].

The details of study endpoints, including instruments, scoring rules, directionality, and primary timepoints are provided in Supporting Information (S1 Table).

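### The comparison of HRSN screening and referral draws on different sources in each arm: the EHR items record clinic activity and will largely miss DAPHNE's own screenings and community referrals, and calls on outside services are stated for the control arm only

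*Protocol article*

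**What the plan says.** **EHR items.** Under Contamination and standard care, EHR abstraction covers "HRSN screening and referrals (social work encounters) for all participants", so referral is read as a social work encounter. Exploratory outcomes repeats this: "Electronic health record (EHR) data will be extracted to capture documentation of HRSN screening and referrals", with abstraction at 3 and 6 months "to capture pediatric primary care visits, social work referrals, and emergency department utilization". The planned use is that "descriptive comparisons between the DAPHNE and standard care arms will be conducted to identify patterns in service utilization and associated costs". The abstract lists the same EHR measures as secondary.

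**What DAPHNE does, and where it is recorded.** Under Scope of HRSN and DAPHNE chatbot, "referrals are limited to domain-specific community resources retrieved through a community resource database". Under Secondary outcomes, the system logs hold items such as "session durations, screenings completed, and resources accessed", and they serve as measures of caregiver engagement.

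**Services outside the EHR.** Contamination and standard care continues: "Follow-up calls with caregivers in the standard care arm will capture services received outside the health system". Its own example is a community-based referral that the EHR does not document. The paragraph ends: "These procedures will allow comparison of intervention and standard care exposure".

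**The concern.** DAPHNE exists to identify needs and to point caregivers to community resources. The EHR items record a different process, namely clinic screening and social work contact. The protocol itself accepts that community referrals can be absent from the EHR. It plans calls to recover them, but states those calls for the standard care arm only. As written, controls are measured by EHR plus calls. The DAPHNE arm is measured by EHR, with logs held apart as engagement. No section defines one screening or referral measure alike in both arms.

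The pilot is meant to inform later choices. The third study objective concerns comparators and outcomes for future trials. Future directions would choose a target domain partly by how referrals respond, and expects referral uptake as a likely secondary outcome of the next trial. A contrast built from unlike sources is a poor guide to either.

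**Working it through.** **The plan's own figures.** None is given for EHR screening or referral. The one precision figure for a proportion is the Wilson interval for 70% retention with n = 100. It reproduces: 60.4% to 78.1%, half-width 8.8 points against the stated 9 or so. It does not bear on this point, so what follows only illustrates direction.

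**Assumed inputs (none from the documents).**
- c = share with a social work referral under standard care, 20–40%
- b = share of the DAPHNE arm referred by the chatbot, 40–60%, independent of c
- s = share of chatbot-referred caregivers' social work encounters that no longer happen
- e = share of the DAPHNE arm's remaining caregivers who gain a social work contact through escalation, 5–15%
- o = share in either arm with a community referral from elsewhere, left as a symbol

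**1. EHR difference, DAPHNE minus control:** c(1 - bs) - c = -cbs.
- s = 0: 0 points for every c and b.
- s = 0.5: from -(0.2)(0.4)(0.5) = -4 points to -(0.4)(0.6)(0.5) = -12 points.
- s = 1: -8 to -24 points.

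**2. Any-source difference, before controls' outside referrals:** c + (1 - c)b - c = (1 - c)b.
- Smallest: (0.6)(0.4) = +24 points. Largest: (0.8)(0.6) = +48 points.
- It does not depend on s, because a caregiver whose encounter is displaced is still counted through the chatbot.

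**3. Escalation added, at c = 30% and b = 60%:** the EHR difference is r + (1 - r)e - c, with r = c(1 - bs).
- s = 0: r = 0.30, so the difference is 0.70e, or +3.5 to +10.5 points.
- s = 0.5: r = 0.21, so the difference is 0.21 + 0.79e - 0.30, or about -5 to +3 points.

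The sign can go either way.

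**4. Unequal ascertainment of outside referrals** (s = 0, e = 0, o the same in both arms and independent).
- EHR plus calls in controls against EHR alone in DAPHNE: c - [1 - (1 - c)(1 - o)] = -(1 - c)o. This is negative for any o above 0, whatever the chatbot does.
- EHR plus log in DAPHNE against EHR plus calls in controls: (1 - c)(b - o).
- EHR plus log in DAPHNE against EHR alone in controls: (1 - c)b.
- All sources in both arms: (1 - c)(1 - o)b.

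The second falls short of the last by (1 - c)o(1 - b). The third exceeds it by (1 - c)ob. Simply adding the log to the EHR and leaving out the calls would therefore favour DAPHNE.

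**5. Noise.** With 50 per arm and 30% in each, the 95% half-width of a difference is 1.96 × √(2 × 0.3 × 0.7 / 50) = about 18 points. Most of the EHR differences above would be within sampling error. The problem is what the contrast means, more than how it would test.

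**The case against.** The strongest reply is that the EHR is not the sole basis of comparison. The exposure comparison follows a sentence on calls, the logs record DAPHNE's side, and interviews in both groups will compare resources received. The EHR items are worded as documentation and social work referrals, and nowhere as total referral received. The outcome is exploratory and descriptive under Exploratory outcomes. No feasibility benchmark uses it, and the next trial's named endpoint is caregiver-reported unmet need. Scoring details are deferred to a supporting table that is not shown.

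Most of this stands, and it limits the consequence. It does not remove the gap: the calls cover one arm, the logs the other, and the interviews involve a few caregivers. The HRSN screener given to both arms measures needs, not screening or referral received.

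Three stronger readings are tempting, and the documents do not support them.
- *A caregiver served by DAPHNE counts as neither screened nor referred.* The intervention arm also receives standard care. Urgent needs may be coordinated with social work, and chatbot-identified needs and referrals are reported to providers, so some DAPHNE-triggered activity may reach the EHR. That the chatbot writes nothing there directly is inferred from silence.
- *The comparison must make DAPHNE look worse.* That requires displacement of social work. The rationale does expect less provider burden, but the protocol says that the tool complements care and does not replace it. Escalation could push the EHR difference upward.
- *An EHR-or-log composite is enough.* It would drop controls' outside referrals, as step 4 shows.

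**Conclusion.** The point holds as one of unequal and partial ascertainment. The EHR items measure clinic-documented screening and social work contact. They will largely miss what DAPHNE itself delivers, and the additional sources differ by arm. A null, lower or higher EHR value in the DAPHNE arm would not show whether caregivers were screened or referred more or less overall.

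No size can be taken from the documents. Under the assumed rates, an EHR difference of 0, or of -4 to -12 points with half displaced, can sit beside an any-source difference of +24 to +48 points. The latter shrinks by the factor (1 - o) once outside referrals are counted in both arms. These figures assume independence of the sources and count referrals issued. The change is worth making because it is cheap and improves what the pilot can say about referral. The primary outcomes and the decision to progress are not affected.

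**What to change.** 1. **Contamination and standard care:** ask the same follow-up question on outside services and community referrals in both arms. It can join the cross-exposure questions already put to participants at 1, 3 and 6 months.
2. **Exploratory outcomes:** label the EHR items as clinic-documented screening and social work contact.
3. **Exploratory outcomes:** add two descriptive measures for both arms, any-source screening and any-source referral, built from the EHR, caregiver report in both arms, and the chatbot log. Show each source separately as well. State that log referrals are referrals issued, not services received.
4. Reconcile the abstract, which calls the EHR measures secondary, with the section that calls them exploratory.

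**Cost:** one added question in the intervention arm, linkage of logs to the EHR extract by study ID, and a few descriptive rows. Enrolment is under way according to Study status and timeline, and caregiver report that is not collected at follow-up may be lost, so the question should be added soon.
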